#### Data collection and confidentiality

To promote participant retention and complete follow-up, we will add WeChat and record the mobile phone number of each participant, and investigators will phone contact or send a text message to remind the participants to follow up before each study visit. The investigators will contact participants who default a scheduled appointment to re-arrange another appointment within 1 week. In addition, we will ask each participant about their compliance with compression therapy (one of the secondary outcomes) to assess whether participants discontinue or deviate from intervention protocols. Participants will be allocated an individual trial identification number according to the order of inclusion. The anonymized trial data will be shared with other researchers to enable international prospective meta-analyses. Information will be entered by Epidata 3.1 in pairs to ensure its quality.

All information collected for this study, including electronic versions (stored on USB sticks) and paper questionnaires, will be securely stored in password cabinets at each center for at least 10 years. Data collected during the research will be kept strictly confidential and only accessed by members of the trial team (or individuals from the Sponsor organization or center sites where relevant to the trial).

#### Data monitoring, safety, and quality control

The ethics committee of each center will audit trial conduct as the circumstances may require. Trial Management Group will meet to review trial conduct per month. The Trial Steering Group and the independent Data Monitoring meet to review conduct throughout the trial period.

No significant adverse events are expected. An adverse event (AE) is an untoward medical occurrence in a patient or clinical study subject, which may or may not be caused by the investigational device. All such events, whether expected or not, should be recorded. A severe adverse event (SAE) is an untoward and unexpected medical occurrence or effect that results in death or is life-threatening, explicitly referring to an event in which the subject was at risk of death at the time of the event. It does not refer to an event that hypothetically might have caused death if it were more severe, requires hospitalization or prolongation of existing inpatients’ hospitalization, results in persistent or significant disability or incapacity, or results from a congenital anomaly or congenital disability. All AEs should be reported as following procedures.

An SAE form should be completed and sent by fax or email to the chief investigator within 24 h. All SAEs should be reported to the Research Ethical Committee where, in the opinion of the chief investigator, the event was “related” (i.e., resulted from the administration of any of the research procedures) and “unexpected” (i.e., an event that is not listed in the Protocol as an expected occurrence). Reports of related and unexpected SAEs should be submitted within 15 days of the chief investigator’s awareness of the event, using the NRES SAE form for non-IMP studies. Local investigators should report any SAEs as required by their Local Research Ethics Committee, sponsor, and/or Research and Development Office.

The investigator and sponsor will do their best to prevent possible injury caused by the design of this study. In case of any injury related to this study, the sponsor will bear the corresponding treatment costs and make compensation by national laws and regulations. If an adverse event caused by the investigational compression treatment causes harm, the clinical research institution and the investigator will provide timely and adequate treatment and management according to the routine clinical treatment.

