#### Secondary outcomes

The secondary outcomes include the following:PainPatients will be asked to record pain scores with VAS, and the scale ranges from 0 (no pain) to 10 (worst pain imaginable) [26].Quality of lifePatients will be asked to fill out the AVVQ to measure the health status of varicose vein patients based on symptoms and impact on daily activities. A total score ranging from 0 to 35, with 35 being the worst quality of life [27].Venous clinical severityPatients will be asked to fill out the VCSS to evaluate the severity of the hallmarks of venous disease. The questionnaire consisted of ten questions, each of which was answered by 0 (none), 1 (mild), 2 (moderate), and 3 (severe)—a total score ranging from 0 to 30, with 30 being the worst quality of venous disease [28].Postoperative complicationsPostoperative complications include postoperative edema, ecchymosis, sensory abnormalities, skin burns/discoloration, phlebitis, hematoma, infection, deep vein thrombosis, and pulmonary embolism.Time to return to regular workThe investigator will use a uniform question to ask the patient how long it takes to return to regular work, life, or both (days), and then record.ComplianceCompliance refers to the extent to which patients follow compression therapy as recommended by their clinicians. Investigators will ask patients whether they have completed compression treatment as recommended by their doctors in the past week or 3 months. The answer to this question involves 1 (none), 2 (occasionally), 3 (mostly), and 4 (entirely). Those who still need to fully follow the study protocol for compression treatment should continue to be asked about their actual compression treatment and recorded.

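### As written, the SAE definition covers only unexpected fatal or life-threatening events; hospitalization, disability and congenital anomaly fall in a list of things it does not refer to

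*Protocol article*

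**What the plan says.** All references are to the protocol article; unless stated otherwise, the text is in the section *Data monitoring, safety, and quality control*.

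- **Definition:** "A severe adverse event (SAE) is an untoward and unexpected medical occurrence or effect that results in death or is life-threatening". The sentence goes on to explain that the subject must have been at risk of death at the time of the event.
- **Next sentence, start:** "It does not refer to an event that hypothetically might have caused death if it were more severe, requires hospitalization or prolongation".
- **Same sentence, end:** "results in persistent or significant disability or incapacity, or results from a congenital anomaly or congenital disability".
- **Recording of adverse events in general:** "All such events, whether expected or not, should be recorded".
- **Expedited step:** "An SAE form should be completed and sent by fax or email to the chief investigator within 24 h".
- **Ethics reporting:** SAEs go to the ethics committee within 15 days if the chief investigator judges them both related and unexpected. Unexpected is explained there as "an event that is not listed in the Protocol as an expected occurrence".
- **General expectation:** "No significant adverse events are expected".

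*Secondary outcomes* lists the postoperative complications to be measured, ending with "phlebitis, hematoma, infection, deep vein thrombosis, and pulmonary embolism". *Objectives* gives essentially the same list.

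**The concern.** A seriousness definition decides which events leave the ordinary case record and reach the chief investigator within a day. Here the sentence that should only clarify what *life-threatening* means has absorbed the other criteria. On its grammar, an event that puts a participant in hospital or leaves a lasting disability is something the term SAE does not cover.

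A second fault sits in the same definition: an event must be unexpected to be an SAE at all. Seriousness and expectedness answer different questions, and the next paragraph treats them as different.

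At stake is prompt notification of serious events, and a consistent SAE count across nine hospitals, in a trial that tests shorter compression and names DVT and PE among the complications of interest.

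**Working it through.** No arithmetic on rates or sample size applies. The check is a reading of the text, in four steps.

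**Step 1. Which criteria stand, and which are excluded?**

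| Criterion named | Where it stands | Status as written |
|---|---|---|
| Death | Defining sentence | Included, if unexpected |
| Life-threatening | Defining sentence | Included, if unexpected |
| Hospitalization or its prolongation | Sentence on what the term does not refer to | Excluded |
| Persistent or significant disability/incapacity | Same sentence | Excluded |
| Congenital anomaly | Same sentence | Excluded |

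That is 2 included + 3 excluded = 5 named, counting hospitalization and its prolongation as the single item they form in the text. Congenital anomaly has little practical weight because *Exclusion criteria* rules out pregnancy and breastfeeding. The criteria that matter in practice are hospitalization and disability.

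**Step 2. Does anything else in the article restore them?** No.

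- The clause on reporting by local investigators speaks of SAEs, so it depends on the same definition.
- The statement that all adverse events are to be reported points to the procedures that follow, and the detailed procedures that follow concern SAEs.

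**Step 3. Is the expectedness condition coherent?** If every SAE were unexpected by definition, the ethics rule's restriction to unexpected SAEs would remove nothing. The rule makes sense only if some SAEs can be expected, which the definition forbids. The two paragraphs therefore conflict.

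Nor does the text settle which events are expected. The test is whether an event is listed as an expected occurrence. DVT and PE are listed as complications to be measured, without being called expected, and the safety section says that "No significant adverse events are expected".

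**Step 4. What happens to particular events?**

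| Event | SAE as written? | 24 h form | Still recorded? |
|---|---|---|---|
| DVT or PE admission, no threat to life | No, whether expected or not | Not triggered | Yes: adverse event and secondary outcome |
| Disabling injury, no threat to life | No, whether expected or not | Not triggered | Yes: adverse event |
| Fatal or life-threatening PE | Yes, if judged unexpected; the text does not settle this | Depends on that judgment | Yes: adverse event and secondary outcome |

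The first two rows do not depend on the expectedness question. They follow from Step 1 alone.

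**The case against.** **The strongest reply is that this is a visible drafting slip.** A clarification of *life-threatening* has run into the rest of the list, and an experienced investigator would probably see what was meant. The article condenses a full protocol that is available on request, and the SAE form itself is not shown, so whether sites work from this sentence cannot be established. That limits what can be said about site behaviour. It does not repair the definition: nothing is merely left out here, because the article states an operative rule and states it wrongly. The unexpectedness condition is also not a matter of punctuation.

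**A reader might infer that the between-arm comparison of complications would be incomplete.** The document does not support this. Complications, including DVT and PE, are a secondary outcome and are asked about at 1 week and 3 months (*Follow-up*), and all adverse events are to be recorded whether expected or not. That comparison does not depend on the SAE label.

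**A reader might also infer that DVT and PE fail the unexpectedness condition because the protocol lists them.** This does not follow. Measuring a complication is not the same as declaring it expected, and the statement that no significant adverse events are expected points, if anything, the other way. What stands is that the matter is unclear.

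**Finally, one might conclude that the data monitors would see too few serious events.** The article says only that the steering and monitoring groups review conduct. It does not say which listings they receive, so this remains conjecture.

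**Conclusion.** The point holds as an error in an operative safety rule. Read as written, an SAE is only an unexpected event that is fatal or life-threatening. Three of the five named criteria are excluded, two of them of practical weight in this population, and expectedness is applied twice in ways that conflict.

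The consequence is limited to SAE classification, SAE counts, 24 h notification and ethics reporting. Data capture, the comparison of complications, the primary endpoint, the non-inferiority test and the sample size are untouched.

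The conclusion assumes that sites apply the definition as published. If the full protocol or the SAE form carries a correct definition, the practical effect shrinks to an error in the published text. It is still worth correcting, because reporting for participant protection rests on this paragraph.

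**What to change.** Reword the definition in *Data monitoring, safety, and quality control*:

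1. Let the remark about events that might hypothetically have caused death qualify *life-threatening* only.
2. List hospitalization or its prolongation, persistent or significant disability or incapacity, and congenital anomaly as separate seriousness criteria alongside death and threat to life.
3. Write *serious* instead of *severe*, since the criteria describe seriousness and not intensity.
4. Remove *unexpected* from the definition. Keep expectedness only as a filter for ethics reporting, and state there which events count as expected, so that the status of DVT and PE is explicit.
5. *Trial status* gives the first enrolment as May 22, 2023, so ask sites to re-check events already recorded against the corrected definition.

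The cost is a one-paragraph amendment, a note to the nine hospitals and one review of recorded events. Design, sample size and analysis do not change.

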#### Publication of data and reproducible research

The findings from this study will be presented locally within the hospitals, published in a peer-reviewed journal, and presented at national and international conferences. The datasets analyzed during the current study and statistical code are available from the corresponding author on reasonable request, as is the full protocol.

#### Availability of data and materials

All data analyses and manuscripts produced will be available on request.

#### Dropout and discontinuation

Patients may voluntarily withdraw from the study for other treatments or no reason, or if a significant safety event occurs and the investigator deems it necessary to stop the trial, the subject may withdraw. However, participants are not encouraged to withdraw from the study voluntarily, and we will be fully prepared for the possibility of adverse events.

#### Ethical approval and study registration

The study has been approved by the Ethical Committee of The Fourth Affiliated Hospital Zhejiang University, School of Medicine (Approval NO.: K2023047). Written, informed consent to participate will be obtained from all participants. The study has been registered at the ClinicalTrials.gov website (https://beta.clinicaltrials.gov/study/NCT05840991). The study will follow the recommendations for physicians involved in research on human subjects adopted by the 18th World Medical Assembly, Helsinki 1964, and later revisions.

#### Protocol amendments

Notifying sponsor and funder first, then the PI will notify the centers, and that a copy of the revised protocol will be sent to the PI to add to the Investigator Site File. Any deviations from the Protocol will be fully documented using a breach report form, and the protocol will be updated in the clinical trial registry.

### Discussion

Although elastic bandages and compression stockings have been widely used for compression therapy after thermal ablation of varicose veins, prolonged compression therapy harms patients’ quality of life and finance. With the development of relevant clinical trials, it has been shown that prolonged compression therapy has no significant clinical gain and may be an unnecessary adjunctive treatment after thermal ablation. The target vein occlusion rate is a crucial concern for vascular surgeons, and simplifying the current compression therapy while ensuring the closure of the treated vein will significantly improve the quality of life and compliance of patients after surgery, reduce their economic burden, and help patients return to everyday life as soon as possible. Suppose the effect of short-term compression therapy proves to be non-inferior to long-term compression therapy. In that case, this trial may contribute to future updates of clinical guidelines for compression therapy after thermal ablation of varicose veins.

### Trial status

Study Protocol Version 1.0, dated March 15, 2023. Recruitment is ongoing, the first patient was enrolled on May 22, 2023, and recruitment is estimated to be completed on August 31, 2023.

## Abbreviations

HL/S: High ligating/stripping
RFA: Radiofrequency ablation
EVLA: Endovenous laser ablation
UGFS: Ultrasound-guided foam sclerotherapy
ABI: Ankle-brachial index
CEAP: Clinical–Etiological–Anatomical–Pathophysiology
VAS: Visual analog scale
AVVQ: Aberdeen Varicose Vein Questionnaire
VCSS: Venous Clinical Severity Score
